### Procedures

#### Data collection

Genetic counseling providers who meet the eligibility criteria and provide written consent will complete a 15-min baseline survey online before their first recorded appointment with a participating patient. The provider baseline survey is designed to assess all four types of bias as well as covariates that are likely to be associated with patient-provider communication, clinical discussion, and/or patient-centered outcomes, including demographic information, professional information, and prior training experiences. Genetic counseling providers will also complete a 1-min post-encounter survey after each genetic counseling encounter with a participating patient. Patients who meet the eligibility criteria will complete a 45-min baseline survey over the phone following the consent and HIPAA authorization and before the scheduled appointment with their participating genetic counseling provider. The patient baseline survey is designed to assess covariates that are likely to predict patient-provider communication, clinical discussion, and/or patient-centered outcomes. After their appointment, patients will complete a 5-min post-encounter survey. Table 2 provides an overview of the variables assessed in the surveys.

**Table 2 Tab2:** An overview of the variables assessed in the surveys

	Genetic counseling providers	Patients
**Baseline**	• Demographic information • Professional information • Implicit racial prejudice • Explicit racial prejudice • Implicit racial stereotyping • Explicit racial stereotyping	• Demographic information • Socioeconomic information • Perceived racial discrimination • General trust in genetic providers • General satisfaction with healthcare
**Post-encounter**	• Therapeutic alliance	• Therapeutic alliance • Provider-specific trust • Provider-specific satisfaction • Perceived empowerment
**Medical chart**		• Genetic test uptake

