### Genetic counseling provider post-encounter survey

#### Therapeutic alliance

We will assess a provider’s perception of the strength of the relationship with a patient using the Working Alliance Inventory-Short Form Revised (WAI-SR) (Therapist). This 12-item measure assesses three domains: goals of the genetic counseling session, tasks to achieve those goals, and bond between the provider and patient. The WAI-SR has high internal consistency (*α* = 0.91) and correlates well with other measures of therapeutic alliance [89]. The response items will range from 1 (Strongly disagree) to 5 (Strongly agree).

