#### Decision about genetic testing

Genetic counseling providers will be asked to indicate whether their patient made a decision about genetic testing during the genetic counseling session using the following options: [1] yes, and they decided to take genetic testing; [2] yes, and they decided not to take genetic testing; [3] no, they need more time to think about it; and [4] no, I did not offer genetic testing.

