Continuous: Likert scale	*Patient-provider communication* (Provider communication style; The overall quality of patient-provider communication)	Linear regression with GEE
Continuous: Frequency	*Patient-provider communication* (Each type of silence; Each type of adjacency pairs; Each type of problems)	Poisson regression with GEE
Continuous: Proportion	*Patient-provider communication* (Topics initiated by providers; Primary units allocated to providers; Silence followed by provider talks; Repairs initiated by providers; Problems repaired by providers)	Linear regression with GEE
Continuous: Duration	*Patient-provider commu*nication (Each type of silence) *Clinical discussion con*tent (The amount of time spent on discussing a given topic)	Linear regression with GEE
Dichotomy	*Clinical discussion content* (The presence/absence of a given discussion topic)	Logistic regression with GEE
Multiple categories	*Patient-provider communication* (The primary units of turns)	Multinomial logistic regression with GEE

Finally, Aim 4 (to quantify the impact of patient-provider communication/clinical discussion content with patient-centered outcomes) examines Paths E and F in our conceptual model. The analyses will be carried out in steps similar to those in Aim 3. In Step 1, we will identify covariates associated with patient-centered outcomes by computing correlations among all aspects of patient-provider communication/clinical discussion topics and factors assessed in the patient baseline survey, the provider baseline survey, and the provider post-encounter survey. In Step 2, we will compute partial correlations between all aspects of patient-provider communication/clinical discussion topics identified in Aims 1 and 2 and patient-centered outcomes while controlling for covariates identified in Step 1. In Step 3, we will conduct a linear regression with GEE and Bonferroni correction for each self-reported outcome (e.g., trust, satisfaction, therapeutic alliance) and a logistic regression with GEE for behavioral outcome (genetic testing completion). All regressions will include the same set of predictors (aspects of patient-provider communication/clinical discussion topics that remain significant in Step 2, and care modality) and covariates. Aspects of patient-provider communication/clinical discussion topics that remain significant in Step 3 are considered as potentially important intervention points for reducing racial disparities in patient-centered outcomes.

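### Aim 4 lets two measures taken after the encounter, provider-rated alliance and the in-session testing decision, compete as covariates for effects they may transmit

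*Protocol article*

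**What the plan says.** Aim 4 relates aspects of communication and discussion topics to trust, satisfaction, therapeutic alliance, empowerment and testing completion. Its analysis has three steps (Protocol article, Statistical analysis).

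- **Step 1** sets out to find covariates of the patient-centered outcomes, but does so by "computing correlations among all aspects of patient-provider communication/clinical discussion topics and factors" drawn from three surveys: "factors assessed in the patient baseline survey, the provider baseline survey, and the provider post-encounter survey".
- **Step 2** computes partial correlations between the communication and discussion variables and "patient-centered outcomes while controlling for covariates identified in Step 1".
- **Step 3** fits one regression per outcome, all with the same predictors and covariates. Terms still significant are read as possible points for intervention.

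On timing, Data collection states: "Genetic counseling providers will also complete a 1-min post-encounter survey after each genetic counseling encounter with a participating patient". On content, the section on that survey describes two measures. The first is the 12-item WAI-SR (Therapist), rating the provider's "perception of the strength of the relationship with a patient". The second asks "whether their patient made a decision about genetic testing during the genetic counseling session using the following options", with four answers covering a decision for testing, a decision against, a need for more time, and testing not offered. Table 2 lists only the alliance for this survey.

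For Aims 1 to 3 the same section draws covariates from the baseline surveys alone.

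**The concern.** A covariate measured after the exposure, and affected by it, does not remove confounding. It removes whatever part of the effect passes through it. The Background section places communication and clinical discussion first, then the patient's perception of the counselor and encounter (Paths E and F), then patient-centered outcomes (Path G). Alliance and the testing decision both come after the communication in that ordering.

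The problem is sharpest in two models. For testing completion, the covariate would be the provider's report of the decision that precedes completion. For patient-rated alliance, it would be the provider's rating of the same construct.

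The wording of Step 1 makes it worse. The stated purpose is association with outcomes, but the operation described is correlation with the exposures, and a consequence of communication is just what such a screen tends to find. A covariate admitted there acts twice: in Step 2, which decides what reaches Step 3, and again in Step 3. Because surviving terms become intervention targets, and the Discussion foresees a list of topics that could be left out of sessions, an association lost through over-adjustment could mislead later work.

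**Working it through.** The plan states no Aim 4 effect size, so there is no figure to reproduce. The check has a textual part and an illustrative part.

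**Text set side by side**

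1. Timing: the provider post-encounter survey follows the encounter (Data collection), while the exposures are coded from the encounter itself. Every variable from this survey is therefore post-exposure.
2. Content: alliance and the testing decision are the only measures described. Naming this survey as a source adds no pre-encounter variable.
3. Role: therapeutic alliance and testing completion are named Aim 4 outcomes (Methods, aims; Statistical analysis).
4. Comparison: Aims 1 to 3 use baseline surveys only, so the choice is specific to Aim 4.

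**Illustration: continuous outcome**

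Input from the document: 220 patients. Assumed: standardised communication score C; alliance M = a·C + noise, variance 1; outcome Y = c·C + b·M + noise with SD 0.8; direct effect c = 0.10; b = 0.40; a = 0.2, 0.3 or 0.5. Patients are treated as independent, with ordinary least squares, two-sided alpha 0.05, no Bonferroni correction, and a screen at p < 0.05 for C against M (Aim 4 states no threshold).

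- Effect without M: c + a·b = 0.10 + 0.2×0.40 = 0.18; 0.10 + 0.3×0.40 = 0.22; 0.10 + 0.5×0.40 = 0.30.
- Effect adjusted for M: c = 0.10 in each case.

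| a | M passes screen | Estimate without M (power) | Estimate with M (power) |
|---|---|---|---|
| 0.2 | 86% | 0.18 (84%) | 0.10 (44%) |
| 0.3 | >99% | 0.22 (96%) | 0.10 (41%) |
| 0.5 | 100% | 0.30 (>99%) | 0.10 (36%) |

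If alliance and outcome also share an unmeasured cause with loading u = 0.4 on each, the adjusted coefficient is c − u²·a/(1 − a²):

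- a = 0.2: 0.10 − 0.16×0.2/0.96 = 0.07
- a = 0.3: 0.10 − 0.16×0.3/0.91 = 0.05
- a = 0.5: 0.10 − 0.16×0.5/0.75 = −0.01

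Simulated means were 0.066, 0.046 and −0.009.

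**Illustration: testing completion**

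Assumed: communication acts only through the decision; log-odds of deciding to test = 0.8 + β·C; completion 90% among those who decide to test and 10% otherwise; 220 independent patients; ordinary logistic regression.

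| β per SD | Odds ratio without decision (rejection rate) | Odds ratio with decision (rejection rate) |
|---|---|---|
| 0.3 | 1.26 (35%) | 1.00 (5%) |
| 0.5 | 1.47 (75%) | 1.02 (4%) |
| 0.7 | 1.70 (94%) | 1.02 (6%) |

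With the decision in the model, rejection stays near the nominal 5%, although communication does change completion in this set-up.

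**The case against.** The strongest reply is that these variables are only candidates. They enter if the screen picks them, so a reader who infers that Aim 4 certainly adjusts for its own consequences goes further than the text. That stands, and the point is conditional. It is not thereby harmless: the described screen favours such variables, and nothing excludes them.

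A second reply concerns the target. The abstract and the Discussion speak of features directly linked to patient-centered outcomes, so a direct effect may be meant. No such estimand is defined, though, and Aim 4 is introduced in the Statistical analysis as quantifying impact. What stands is that adjustment would not remove the whole effect: any direct part remains, as the 0.10 above shows.

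Third, Table 1 lists the provider post-encounter survey as an Aim 4 data source, which by itself could mean that alliance is an outcome. Step 1, however, explicitly uses the survey for covariates.

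Fourth, Step 1 may be compressed article wording for a screen against outcomes. That is possible, and it is then only a possibility that outcome predictors such as general trust or baseline empowerment are missed. The post-encounter survey would remain in the pool, and alliance and the decision would be likely to correlate with the outcomes too.

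Two stronger readings are tempting and unsupported.

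- **Near-separation in the completion model.** If 95% of those deciding to test and 5% of the others completed, the decision would carry an odds ratio of (0.95/0.05)/(0.05/0.95) = 361. Those rates are assumed, and the figure describes the decision–completion link, not bias in the communication effect. With an even split of 220 (also assumed), each discordant cell holds 110×0.05 = 5.5 patients, so the model can be fitted.
- **Sign reversal.** The most adverse case above reaches only −0.01, and only with an added unmeasured common cause.

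**Conclusion.** The concern holds as a conditional one. Step 1 of Aim 4 admits as candidate covariates two measures that the protocol's own model places after the exposures, and its wording makes their selection likely. If they are selected, the Aim 4 associations shrink toward their direct part, and toward null where the effect runs through the decision or the alliance. Because the Step 3 models share one covariate set, selection would carry into every outcome model.

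The direction for a mediated effect follows from the structure; the size does not. Under the assumed paths, 0.18 to 0.30 becomes about 0.10, and odds ratios of 1.26 to 1.70 become about 1.0. These figures ignore clustering by provider, the Bonferroni correction and the other covariates, and the documents supply none of the path strengths. Certain adjustment, near-separation and sign reversal are not established. The defect concerns one of four aims in an observational study, but it touches the estimates from which that aim would name intervention points.

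**What to change.** In Aim 4, Step 1:

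- Remove the provider post-encounter survey from the list of covariate sources, and state that only variables measured before the encounter qualify, as in Aims 1 to 3.
- Reword the screen so that candidates are correlated with the patient-centered outcomes, which is the purpose Step 1 gives. Include the planned baseline counterparts where they exist: general trust for provider-specific trust, baseline GOS for empowerment, and general satisfaction with healthcare for encounter satisfaction. Alliance and testing completion have no such counterpart.
- Analyse provider-rated alliance and the in-session decision as outcomes, or as mediators in a separate analysis labelled as estimating a direct effect.

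Replacing the screen with a fixed covariate set is a further design choice and is not needed to cure this defect. The cost is a few sentences of analysis wording. All variables are already planned, so no new data, visits or patients are required.

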## Methods

The overarching goal of this research is to compare and contrast the nature of cancer genetic counseling encounters and patient-centered outcomes between Black and White patients in the naturalistic clinical setting. We will test our hypotheses by addressing four specific aims: **Aim 1**) To compare/contrast the nature of patient-provider communication by patient race (Black vs. White); **Aim 2**) To compare/contrast the clinical discussion content by patient race; **Aim 3**) To quantify the role of each type of counselor bias in patient-provider communication (Aim 1) and clinical discussion content (Aim 2); and **Aim 4)** To quantify the role of patient-provider communication and clinical discussion content with patient-centered outcomes (trust, satisfaction, therapeutic alliance, empowerment, genetic testing completion). These aims will be achieved through an observational study with a convergent mixed methods research design. Table 1 provides an overview of the study design.

**Table 1 Tab1:** An overview of the study designs

Aims	Data sources	Analyses	Goals
1	• Recorded encounters	Quantitative analyses of provider communication style and the overall quality of patient-provider communication Qualitative analyses of transcribed encounters for the four basic interaction structures	Identify specific aspects of patient-provider communication during cancer genetic counseling encounters that are different between Black and White patients
2	• Recorded encounters	Qualitative analyses of transcribed encounters for (1) the presence/absence of the key topics for risk communication and genetic test consent during cancer genetic counseling encounters that were identified by NCI; and (2) additional topics discussed during cancer genetic counseling encounters	Identify specific clinical discussion topics during cancer genetic counseling encounters that are different between Black and White patients
3	• Provider baseline survey • Patient baseline survey • Coded encounters	Quantitative analyses of associations between the four forms of provider bias and (1) patient-provider communication as well as (2) clinical discussion content that were identified in Aims 1 & 2	Identify specific aspects of patient-provider communication/clinical discussion topics that contribute to racial disparities in the cancer genetic counseling process and reflect provider bias

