To assess *the linguistic patterns of* patient-provider communication, we will both observe recordings and analyze transcripts. Specifically, we will examine genetic counseling providers’ linguistic patterns that reflect constructs associated with levels of implicit prejudice during racially discordant interactions in prior research, including social dominance, [52, 53] intergroup anxiety, [54–56] and avoidance (or lack of engagement) [57–59]. For social dominance, we will code: [1] patient-provider talk time ratio [25, 60]; [2] frequency of first person plural pronouns [26]; [3] turn-taking ratio [61, 62]; and [4] the number of interruptions and overlapping speech [63, 64]. For intergroup anxiety, we will code: [1] frequency of anxiety-related words (e.g., worried, afraid, nervous); [26] and [2] frequency of hesitation markers (e.g., uh, uhm, umm). For avoidance, we will code: [1] encounter length; and [2] frequency of back-channeling responses (e.g., Okay, yes, ah huh) [65].

Frequencies (i.e., first person plural pronouns, anxiety-related words, hesitation markers, back-channeling responses) will be assessed with the Linguistic Inquiry and Word Count (LIWC) software [66]. Each recording will be first transcribed verbatim, and then the verbatim transcripts will be further edited using the guidelines specifically developed for text analysis using LIWC [67]. Finally, the edited transcripts will be divided into two documents: patient vs. provider speech. The LIWC computes the percentage of use of words in more than 70 + word categories; it also enables researchers to create new word categories. For the current analyses, we will use both existing (i.e., pronouns, affective processes) and new (i.e., hesitation markers, back-channeling responses) categories.

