#### Topic comprehensiveness of clinical discussion

Next, we will assess the extent to which topics discussed during clinical encounters are consistent with key topics included in the National Cancer Institute’s (NCI) Cancer Genetics Risk Assessment and Counseling (PDQ®)-Health Professional Version [70]. To do this, two genetic counselors on our team will create a topic codebook based on the PDQ®-Health Professional Version. The codebook will provide coding procedures and rules as well as descriptions and examples of each topic. While the codebook is being developed, two coders will unitize the verbatim transcripts into discrete topics or focal ideas/themes. The coders will be first trained on the unitization with a few transcripts before they start unitizing all transcripts. They will meet every 5 transcripts to discuss and solve discrepancies in the identified thought units. After all the verbatim transcripts are unitized into discrete topics, two coders will be trained on the codebook until they achieve consensus and then code all transcripts independently, while meeting every 10 transcripts to discuss discrepancies and reach consensus. We will use consensus estimates for two reasons. Methodologically, discussion topics are discrete categories [71]. Clinically, providers are expected to discuss with patients each topic clearly and with no ambiguity. Finally, for each encounter, we will create dichotomous (a given topic discussed/not discussed) and continuous (the total amount of time spent on discussing a given topic in seconds) outcomes.

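### Aim 4 relates testing completion to talk totalled over the whole session, so consent talk that follows a patient's yes can be read as a cause of completion

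*Protocol article*

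**What the plan says.** **Predictors.** In the section on topic comprehensiveness, two coders are to "code all transcripts independently, while meeting every 10 transcripts to discuss discrepancies and reach consensus". The result is that "for each encounter, we will create dichotomous (a given topic discussed/not discussed) and continuous (the total amount of time" on each topic. The time measure is described as "continuous (the total amount of time spent on discussing a given topic in seconds) outcomes". The section on communication quality adds encounter length and "patient-provider talk time ratio". No window within the session is stated for any of these.

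**Content.** Table 1 (Methods) says the coded topics include "key topics for risk communication and genetic test consent". The Methods also describe the recorded pre-test session as the one that includes informed consent.

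**Decision.** The provider post-encounter survey asks "whether their patient made a decision about genetic testing during the genetic counseling session", and the patient survey asks the same of the patient. The answers allow for yes, no, undecided and no test offered. When in the session the decision came is not recorded.

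**Model and use.** Aim 4, Step 3 uses "a logistic regression with GEE for behavioral outcome (genetic testing completion", with completion read from the chart up to 6 months later. What stays significant is to be regarded as a possible target for intervention. The Discussion goes further and foresees lists telling counselors which topics to cover and which to leave out.

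**The concern.** A patient who agrees to testing may trigger further talk about consent details and next steps, while one who declines or defers may not. For that part of the talk, the decision comes before the predictor. Completion follows largely from the decision, so the talk and completion will be associated even if talking changes nothing. GEE handles clustering and Bonferroni handles the number of tests. Neither addresses direction.

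At stake is a training recommendation. Counselors could be told to cover, or spend longer on, content that only marks patients who had already agreed. If acceptance differs by race for other reasons, the same mechanism would also create a race gap in consent talk under Aim 2 and attribute it to the provider.

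**Working it through.** The plan gives no figure for this point. Its only power statement concerns provider implicit prejudice and communication style, so there is nothing to reproduce.

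**Inputs from the article:** 220 patients, 15 providers, logistic GEE, whole-session predictors.

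**Assumed, because the article does not say:** the share saying yes (π), completion after a yes (c1) and otherwise (c0), and the extra consent talk a yes adds (δ, in SD of pre-decision talk). The true effect of talk on completion is zero.

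**1. Hand calculation.** With unit variance, the log odds ratio per SD is roughly δ × [P(yes | completed) − P(yes | not completed)].

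For π = 0.75, c1 = 0.90, c0 = 0.10:
- P(completed) = 0.75×0.90 + 0.25×0.10 = 0.70
- P(yes | completed) = 0.675/0.70 = 0.964
- P(yes | not completed) = 0.075/0.30 = 0.25
- difference = 0.714

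At δ = 0.5 this gives exp(0.357) = 1.43. At δ = 0.25 it gives exp(0.179) = 1.20. At δ = 1.0 it gives exp(0.714) = 2.04, slightly high because the yes/no mix then widens the variance within groups.

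**2. Simulation** (500 datasets per setting, logistic GEE, independence working correlation, robust SE, whole-session talk):

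| π | c1 / c0 | δ | median OR | p<0.05 | p<0.05/20 |
|---|---|---|---|---|---|
| 0.75 | 0.9 / 0.1 | 0 | 0.98 | 8% | 1.2% |
| 0.75 | 0.9 / 0.1 | 0.25 | 1.21 | 29% | 6% |
| 0.75 | 0.9 / 0.1 | 0.5 | 1.43 | 67% | 32% |
| 0.75 | 0.9 / 0.1 | 1.0 | 1.94 | 99.8% | 89% |
| 0.90 | 0.9 / 0.1 | 0.5 | 1.30 | 35% | 9% |
| 0.60 | 0.8 / 0.2 | 0.5 | 1.32 | 56% | 24% |

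The 8% in the first row reflects robust standard errors with only 15 clusters. The divisor of 20 is illustrative.

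**3. Topic presence.** Assume 85% accept, 95% of acceptors complete, no one else completes, and the topic is covered in 80% of acceptors and 60% of others.
- Completers: 0.85×0.95 = 0.8075. Non-completers: 0.15 + 0.0425 = 0.1925.
- Coverage in non-completers: (0.15×0.60 + 0.0425×0.80)/0.1925 = 0.644.
- OR = (0.80/0.20)/(0.644/0.356) = 2.2.

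Simulations at these acceptance and coverage rates, without clustering, gave p<0.05 in about 52% to 55% of datasets.

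**4. Adjusting for the decision.** Adding the in-session decision to the model in step 2 gives p<0.05 in 8% to 10% and median OR 0.99 to 1.01. The false signal goes, but so would any real effect that acts through the decision.

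**5. Cutting deciders at their decision.** In step 2's simulation, using only pre-decision talk gives 6% to 10% (OR 0.99 to 1.02 where a yes adds talk). That simulation does not let the cut shorten the session. If deciders are cut at the decision while undecided patients keep the whole session, presence of unrelated topics is biased the other way. With decisions 30% to 90% through the session, simulations gave median OR 0.56 to 0.67 and p<0.05 in 28% to 56%. With decisions at 80% to 100%, they gave OR 0.84 to 0.87 and 5% to 8%.

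**The case against.** - **The mechanism is not documented.** No sentence says consent content follows a yes, and much of it should precede agreement. The article calls pre-test content more uniform than post-test content and expects providers to cover each topic clearly. This stands as a limit on size. It does not show that no talk follows acceptance.
- **Frequency.** A reader might infer from the two surveys that decisions are often made in session. They only list response options and give no rate.
- **The Step 1 screen may bring in the decision.** Aim 4 draws candidate covariates from the provider post-encounter survey, which contains the decision item. This stands in part: if selected, it would block the false signal. But selection is left to a correlation screen, Table 2 lists only therapeutic alliance for that survey, and adjustment removes the route from discussion through decision to completion.
- **The Aims 1 and 2 filter.** Only aspects identified there reach Aim 4. Assuming acceptance of 85% in White and 55% to 65% in Black patients, and 40 tests, the race gap in consent seconds passed Bonferroni in 2.5% to 33% of simulated studies. The rates under working apply only to a topic that has reached the model. Step 2, however, selects on association with the outcome and so favours such topics.
- **Cautious wording.** The study is observational and its targets are called potential. But Aim 4 also speaks of impact, and the Discussion plans topic lists.
- **A codebook detail.** Marking the decision could be left to the codebook. Which results may be named intervention targets is fixed in the article itself.

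**Conclusion.** The point holds as a risk to interpretation, confined to testing completion and to content that can follow a yes. Predictors are taken over the whole encounter, the decision may fall inside it, and the plan does not separate talk before the decision from talk after it. Whole-session coding is inferred from coding all transcripts and totalling time per topic; no sentence states it in those words.

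A reader might go further and infer that Aim 4 will produce a false claim about consent talk. The documents do not support that. The size depends on four things they do not give: how often patients decide in session, how much consent talk follows a yes, whether the topic passes Aims 1 and 2, and whether the Step 1 screen selects the decision. The range of 29% to 99.8% shows only that moderate amounts of triggered talk would be enough once a topic is in the model.

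**What to change.** 1. During unitization, have the existing coders mark the unit where the patient states a testing decision, and code whether each topic was first raised before or after it.
2. Keep the whole-session completion model and report it as an association.
3. State in Aim 4 that consent or next-step content occurring after acceptance is descriptive and cannot be named an intervention point for completion.
4. For other topics, require that the association is not explained by post-decision talk. Check this in a sensitivity analysis with a cut comparable for all patients, for example talk before the test is offered. Do not truncate deciders only, since that pushes odds ratios below 1. Say how patients who were not offered a test are handled, because they have no such cut.

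The cost is one extra mark and a before/after code per transcript, a few sentences in the analysis text, and fewer topics eligible as intervention points for completion. The mark shows when a decision is stated, so it does not help with patients who arrive already decided.
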